| IEC | Institutional Ethics Committee |
| IDSA | Infectious Disease Society of America |
| NHSN | National Healthcare Safety Network |
| OPD | Out Patient Department |
| POD | Post Operative Day |
| LMIC | Low- Middle Income Countries |
| SD | Standard Deviation |
| SHEA | Society for Health care Epidemiology of America |
| SPSS | Statistical package for the social sciences |
| SSIs | Surgical Site Infections |
| WHO | World Health Organization |

# Protocol Synopsis

| **Study Title** | Impact of multipronged interventions targeting healthcare professionals in reducing surgical site infections and identifying the challenges in adoption of these interventions. |
| --- | --- |
| **Type of study** | Implementation study |
| **Study Rationale** | While the global estimates of SSI vary from 0.5% to 15% depending on type of surgery; the low-middle-income countries including India have disproportionately higher rates of surgical site infections as ranging from 23 to 38% as compared to high-income countries, despite adjustment for the surgery and patient factors. SSI rate may be influenced by various factors like pre-operative care, timing of antimicrobial administration for surgical prophylaxis, patient factors, operation theatre environment, intra-operative conditions, type of surgery, post-operative care and hand hygiene. However, the implementation of these measures has not been standardised due to multiple reasons with some being lack of knowledge in surgeons, rigidity in changing the practice among surgeons and health care professionals despite availability of WHO recommendations.  Recent audits and point prevalence studies in LMICs including India confirm continued high occurrence of multiple doses of antimicrobial surgical prophylaxis for > 1day, which is likely to exacerbate antimicrobial resistance and contribute to added cost of therapy. 48.9% of the ICU patients have apparent inappropriateness in the choice of prophylactic antibiotic. Dual anaerobic coverage in 43.5%, dual gram-negative coverage in 9.7% and overlapping in both gram positive and gram-negative coverages in 4.4% patients. A recent meta-analysis by Cooper L et al (2020) showed that administration of single-dose and short-duration surgical antimicrobial prophylaxis in caesarean section was associated with lower risk of SSI. However, the effect of adoption of optimal surgical prophylaxis remains under-evaluated in other type of surgeries including general surgery. With this background, we plan to develop and assess the effect of multipronged interventions for prevention of surgical site infections in surgical patients. |
| **Study Objective(s)** | **Primary**  To evaluate the effect of multipronged interventions on rate of surgical site infections in clean, clean-contaminated, contaminated surgeries.  **Secondary**   1. To identify the system and behavioral factors contributing to surgical site infections 2. To co-develop multipronged interventions which can be applied in hospital settings 3. To evaluate the impact of multipronged interventions on inpatient mortality and length of hospital stay 4. To evaluate the number of deaths prevented by adoption of multipronged interventions 5. To evaluate the number of ICU admissions averted and number of hospital readmissions averted within 30 days after discharge by adoption of multipronged interventions 6. To evaluate the effect of multipronged interventions on the antimicrobial consumption indicator Days of therapy (DOT). 7. To evaluate the percentage of patients receiving the correct surgical antimicrobial prophylaxis. |
| **Intervention** | Multipronged Interventions (to be co-developed by stakeholders) |
| **Indication** | Prevention of surgical site infections |
| **Study Design** | Mixed methods- Co-development of intervention (Mixed method) followed by Quasi-experimental, pretest-posttest design (Quantitative) and in-depth-interviews of healthcare professionals (Qualitative) |
| **Subject Population**  **key criteria for Inclusion and Exclusion:** | **Inclusion Criteria**   1. Surgical adult patients undergoing elective or emergency procedure (open or laparoscopic) under general surgery, neurosurgery, orthopedics, plastic surgery, urology, pediatric surgery. 2. Aged upto 65 years of age.   **Exclusion Criteria**   1. Pregnant or lactating females 2. Immunocompromised patients including uncontrolled diabetic patients, cancer patients, on immunosuppressive therapy. 3. HIV/HBV/HCV infection 4. Patients with prolonged hospital stay >1 week and received multiple antimicrobials before the planned procedure. 5. Patients with dirty wounds 6. Pre-existing active infection at surgical site 7. Minor procedure performed under local anesthesia 8. Therapeutic hypothermia needed during intra-operative or post-operative period |
| **Number of Participants** | The three types of surgeries (clean, clean-contaminated and contaminated) will be separately powered, based on different baseline SSI rates. The sample sizes were based on 90% power, a 5% two-sided significance level and 15% loss to follow up or death before reaching the primary endpoint at 30-days. For the clean surgeries, anticipating the baseline average SSI rate of 8%, a 3% absolute reduction in SSI to 5% will be taken as clinically significant and would require 3260 patients in total. For the clean-contaminated surgeries, anticipating the baseline average SSI rate of 12%, a 4% absolute reduction in SSI to 8% will be taken as clinically significant and would require 2700 patients in total. For the contaminated surgeries, anticipating higher baseline SSI rate of 30%, a 10% absolute reduction in SSI to 20% will be taken as clinically significant and would require 900 patients in total. |
| **Study Duration** | Each subject’s participation will last for 30 days or 90 days if implant in situ. |
| **Study Phases** | The plan is to adopt a four- phased strategy, each addressing specific research question. Phase-I will involve formative research and practice analysis. Phase-II will involve co-development of the multipronged interventions. Phase-III will involve deployment of the multipronged interventions and process evaluation. Phase-IV will involve impact assessment and dissemination of results. |
| **Primary endpoint** | The rate of surgical site infection till 30 days after surgery (90 days if implant) using CDC definition of SSI in pre-intervention versus post-intervention phase for clean, clean-contaminated and contaminated surgeries |
| **Secondary endpoints** | 1. The number of ICU admissions averted and number of readmissions averted in clean, clean-contaminated and contaminated surgeries by adoption of multipronged interventions 2. The length of index hospital admission in pre-intervention and intervention phase for clean, clean-contaminated and contaminated surgeries. 3. The antimicrobial consumption indicator, Days of therapy (DOT) in the pre-intervention and intervention phase for clean, clean-contaminated and contaminated surgeries. 4. The percentage of patients receiving single dose of antimicrobial prophylaxis in the pre-intervention and intervention phase for clean, clean-contaminated and contaminated surgeries 5. The percentage of patients receiving prolonged antimicrobial prophylaxis (>24 hours duration) in the pre-intervention and intervention phase for clean, clean-contaminated and contaminated surgeries 6. The percentage of irrational combinations of drugs (double gram positive, double gram negative or double anaerobic coverage) for surgical antimicrobial prophylaxis in the pre-intervention and intervention phase for clean, clean-contaminated and contaminated surgeries 7. The number of deaths prevented in clean, clean-contaminated and contaminated surgeries by adoption of multipronged interventions 8. Acceptance of multimodal interventions and challenges in their implementation by healthcare professionals. |
| **Statistical And Analytic Plan** | The data collected in the antimicrobial audit form will be analysed after entry into the excel form. The antimicrobial consumption analysis will be done using Microsoft excel. The descriptive data analysis will be done using Statistical package for the social sciences (SPSS) Version 23. The rate of surgical site infection till 30 days after surgery (90 days if implant) will be expressed as events per person-time, separately for clean, clean-contaminated, contaminated surgeries. All secondary endpoints will be expressed as mean, SD (if the variable is quantitative) or as frequency, percentage (if the variable is categorical). The rates of primary outcome and secondary outcomes measured at the study centres in post-intervention will be compared with the pre-intervention/baseline data to assess the impact of the intervention. Chi-square test, independent sample t test or Mann-Whitney U test will be used for the statistical comparisons.  Plots and pivot tables will be generated using statistical software or excel as appropriate. The analysis will be conducted separately for clean, clean-contaminated and for contaminated surgeries. A sub-group analysis will also be conducted as per the level of fidelity.  Kaplan Meier curves will be plotted to demonstrate the incidence rates of surgical site infections. The difference in the rate of surgical site infections between the nature of surgeries (clean, clean-contaminated, contaminated surgeries), or any other exposure categories will be statistically tested using the log-rank test. A Cox proportional hazard model will be constructed to identify the predictors of surgical site infections. |
| **Safety Evaluations** | The study does not involve any additional risk to baseline the risk of surgery. So, we will request the Ethics Committee (EC) for waiver of the informed consent. |
| **Data And Safety Monitoring Plan** | The study involves low-minimal risk. The confidentiality and anonymity of each patient and their data will be strictly maintained before, during the study and while publication of the study results. |

# Background Information and Rationale

## Introduction and relevant literature

Surgical site infections (SSIs) are defined as the superficial site involving skin and subcutaneous tissue of the incision site within 30 days or deep incisional site infections involving deep soft tissues of the incision (fascial and muscle layers) within 30 or 90 days following the operative procedure with the patient having at least one of the following: (a) purulent discharge from the incision, (b) organism(s) detected from the aseptically obtained wound specimen, (c) evidence of infection or abscess (in case of deep SSI) by clinical examination or at imaging, or incision opened spontaneously or deliberately opened by the clinician/surgeon; and patient had at least one of the following signs and symptoms: localized pain or tenderness, localised swelling, redness, heat at the wound site or systemic fever (>38°C) as per Centres for Disease Control and Prevention (CDC).^1^

The World Health Organization (WHO) mentions SSI as the most common hospital acquired infections (HAI) among surgical patients in low-middle income countries (LMICs) affecting around one third of the patients undergoing surgical procedures.^2^ While the global estimates vary from 0.5% to 15% depending on type of surgery; the LMICs including India have disproportionately higher rates of surgical site infections as ranging from 23 to 38% as compared to high-income countries,^3^ despite adjustment for the surgery and patient factors.^4^ SSIs lead to higher antibiotic consumption, increased medical costs, prolonged hospital stay and recovery time, poor wound healing, risk of wound breakdown and hernia, poor clinical outcomes, psychological challenges and increased mortality. The patients who develop SSI are 60% more likely to be admitted to ICU and have twice the mortality rate than non-infected patients.^3^ It is noteworthy that around 40-60% of SSIs are preventable by use of infection control practices. The Society for Health care Epidemiology of America (SHEA) in collaboration with Infectious Disease Society of America (IDSA), the American Hospital Association (AHA), the Association for Professionals in Infection Control and Epidemiology (APIC) published “Strategies to prevent surgical site infections in acute care hospital” in 2008 and updated in 2016 and WHO provides the guidance to prevent the surgical site infections.^2,5,6^

Despite these guidance documents in place, SSIs remains a substantial cause of morbidity, mortality and economic burden in hospitalized surgical patients especially in LMICs. Recent studies from India showed a comparatively lower yet substantial incidence of SSI of about ~12.5 % in general surgical patients with most common pathogen associated with SSI being beta-haemolytic *Streptococci* and *Staphylococcus aureus*.^7^ The study found that the prevalence of SSI was higher (17.7%) in emergency surgeries as compared to 12.5% in elective surgeries probably requiring judicious and timely use of surgical prophylaxis as per recommendations, extra pre-operative and intra-operative care to lower overall SSI incidence rates.^7^ Similar rates were found in a recent large pragmatic multicentric randomized controlled study in LMICs with overall SSI rate of 22% (15.5% for clean-contaminated and 30% for contaminated or dirty surgeries).^8^ A prospective study conducted recently in PGIMS Rohtak, India found incidence of SSI to be ~8% for clean and ~10% for clean-contaminated surgeries.^9^

SSI rate may be influenced by various factors like pre-operative care, agent and timing of antimicrobial administration for surgical prophylaxis, patient factors, operation theatre environment, intra-operative conditions, type of surgery, post-operative care and hand hygiene.^10^ However, **the implementation of these measures has not been standardised due to multiple reasons** with some being lack of knowledge in surgeons, rigidity in changing the practice among surgeons and health care professionals, inconsistency in interpretation of evidence and WHO recommendations. The WHO describes compliance with current guidelines for antimicrobial surgical prophylaxis, surgical prophylaxis within 60 minutes prior to surgery and surgical prophylaxis stopped within 24 hours after surgery as major process measures in reducing the surgical site infections.^11^ In addition to appropriate use of antimicrobial prophylaxis, other measures like maintaining operation theatre (OT) cleanliness, hand hygiene, aseptic precautions, sterile environment in OT, restricting the opening of OT door are other important measures in limiting the SSIs^12,13^. A recent quality improvement study in cesarian section patients in India showed that quality improvement measures like following standard antimicrobial prophylaxis guidelines, decreasing OT traffic, reduced door openings training of OT staff, surgical safety checklist, and biomedical waste management led to reduction in SSI rate from 30% to 5% over a period of 6 months^14^.

Recent audits and point prevalence studies in LMICs including India confirm continued high occurrence of multiple doses of antimicrobial surgical prophylaxis for > 1day, which is likely to exacerbate antimicrobial resistance and contribute to added cost of therapy.^15,16^ Another study done to see antibiotic prescription practices for surgical prophylaxis in Bangalore, India found that 48.9% of the ICU patients had apparent inappropriateness in the choice of prophylactic antibiotic and only 3.2 % were in accordance with the IDSA guidelines. Dual anaerobic coverage was present in 43.5%, dual gram negative coverage was present in 9.7% and overlapping in both gram positive and gram negative coverages was present in 4.4% of the total 1012 patient ICU days, exposing the patients to higher WHO defined daily doses (DDD) of antibiotics.^17^ A recent meta-analysis by Cooper L et al (2020) showed that education to improve appropriate antibiotic prophylaxis is associated with reduction of SSIs in LMICs.^18^ Even though the sizes of absolute effect were small (risk ratio of 0.77 and 0.89) and not statistically significant, administration of single-dose and short-duration surgical antimicrobial prophylaxis in Caesarean section was associated with lower risk of SSI.^18^

To the best of our knowledge, efficacy of optimal surgical prophylaxis has not been strategically evaluated in other type of surgeries including general surgery. There is evidence in the literature that for surveillance to improve outcomes it needs to be paired with effective audit and feedback mechanism to frontline workers, so that they can change their behaviour in light with the quantitative data of audit and feedback.^13^ However, this alone has not led to significant reduction in the rate of SSIs. Hence, there is a need to co-develop feasible and scalable multipronged interventions, targeting healthcare professionals, system level challenges and contextualised to the logistic constraints of LMICs for prevention of surgical site infections.

# Study Objectives

## Primary Objective (or AIM):

To evaluate the effect of multipronged interventions on rate of surgical site infections in clean, clean-contaminated, contaminated surgeries (Refer to Appendix III for definitions). (Multipronged intervention components mentioned in section 3.6)

## Secondary Objectives (or AIM)

1. To identify the system and health care professional behavioral factors contributing to surgical site infections
2. To co-develop multipronged interventions which can be applied in hospital settings in LMICs
3. To evaluate the impact of multipronged interventions on in-patient mortality and length of hospital stay
4. To evaluate the number of deaths prevented by adoption of multipronged interventions
5. To evaluate the number of ICU admissions averted and number of hospital readmissions averted within 30 days after discharge by adoption of multipronged interventions
6. To evaluate the effect of multipronged interventions on the antimicrobial consumption indicators Days of therapy (DOT).

[Days of therapy is defined as an aggregate sum of days for which any amount of a specific antimicrobial agent was administered to individual patient^13^]

1. To evaluate the percentage of patients receiving the correct surgical antimicrobial prophylaxis.
2. To evaluate the acceptance of these multipronged interventions and challenges in their implementation by health care professionals using in-depth interviews and a qualitative feedback assessment form.

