## Subject Completion/Withdrawal

The patients who take leave from hospital against medical advice (LAMA) will be contacted for follow-up at 30-days for the outcome.

If follow-up is not possible at 30 days after surgery, patients will be followed up as soon after this as possible.

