## Secondary Endpoints

1. The number of ICU admissions averted and number of readmissions averted in clean, clean-contaminated and contaminated surgeries by adoption of multipronged interventions
2. The length of index hospital admission in pre-intervention and intervention phase for clean, clean-contaminated and contaminated surgeries.
3. The antimicrobial consumption indicators (Days of therapy) in the pre-intervention and intervention phase for clean, clean-contaminated and contaminated surgeries.
4. The percentage of patients receiving single dose of antimicrobial prophylaxis in the pre-intervention and intervention phase for clean, clean-contaminated and contaminated surgeries
5. The percentage of patients receiving prolonged antimicrobial prophylaxis (>24 hours duration) in the pre-intervention and intervention phase for clean, clean-contaminated and contaminated surgeries
6. The percentage of irrational combinations of drugs (double gram positive, double gram negative or double anaerobic coverage) for surgical antimicrobial prophylaxis in the pre-intervention and intervention phase for clean, clean-contaminated and contaminated surgeries
7. The number of deaths prevented in clean, clean-contaminated and contaminated surgeries by adoption of multipronged interventions
8. Acceptance of these multipronged interventions and challenges in their implementation by healthcare professionals.

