# STUDY ADMINISTRATION

## Data collection and management

Patients planned for general surgical procedures (elective or emergency) will be screened for inclusion in the study based on inclusion and exclusion criteria.

The data collection during baseline, post-intervention phase for the surgical patients undergoing elective or emergency surgery will be done by the Infection control nurse and research fellow in the standardized data collection form including but not limited to the data on timing of antimicrobial prophylaxis given, time of start of surgery, vitals, re-dosing of antimicrobial prophylaxis, time of stoppage of surgery, type of surgery (name of surgery; clean/clean-contaminated/contaminated/dirty), aseptic precautions taken or not, information on drains in situ, post-operative care, details of post-operative antimicrobials. The patient will be followed up regularly till discharge and data on SSI, antimicrobials, clinical outcome will be recorded. The patient will be called in-person for follow-up to ODP at 30-day to know the clinical status and outcome of the patient. Any unplanned visit to OPD or emergency will be noted with the reason of the visit.

If follow-up is not possible at 30 days after surgery, patients will be followed up as soon after this as possible or telephonically. If patient developed SSI before postoperative day 30, they will still be reviewed at 30 days after surgery to record secondary outcomes.

In intervention phase, in addition the checklist of multipronged interventions will be checked for implementation assurance along with the data collection form.

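### Secondary objective 3 measures mortality over the in-patient stay, a window that changes with length of stay; a fixed 30-day window should be used for all the death measures

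*Protocol*

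**What the plan says.** Section 2.2 sets the objective "To evaluate the impact of multipronged interventions on in-patient mortality and length of hospital stay", and the Synopsis repeats it: "To evaluate the impact of multipronged interventions on inpatient mortality and length of hospital stay". The next objective in Section 2.2 is "To evaluate the number of deaths prevented by adoption of multipronged interventions", with no time window.

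In Section 3.8 the only endpoint concerning death is item 7, "The number of deaths prevented in clean, clean-contaminated and contaminated surgeries by adoption of multipronged interventions", again without a window. In-patient mortality is not in that list. Length of stay is, as item 2: "The length of index hospital admission in pre-intervention and intervention phase for clean, clean-contaminated and contaminated surgeries".

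Follow-up continues after discharge. Section 3.3.1 follows each patient to day 30, or day 90 with an implant. Section 4.1 calls patients back at day 30 "to know the clinical status and outcome of the patient" and says that patients with an earlier SSI are still seen then so that secondary outcomes can be recorded. Section 3.5 says that patients who leave against medical advice (LAMA) "will be contacted for follow-up at 30-days for the outcome".

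**The concern.** In-patient mortality is a count over a window of variable length. The protocol has reason to expect that length to change: it is an outcome in its own right, it shares an objective with mortality, and Section 1.1 states that "SSIs lead to higher antibiotic consumption, increased medical costs, prolonged hospital stay and recovery time". If the package succeeds on stay, each patient is at risk of an in-patient death for fewer days, and some deaths move to after discharge without being prevented.

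The design gives no protection. Section 3.1 is a pre-post comparison, and Section 3.2 describes no allocation and hence no concurrent control. A drift in discharge practice between phases would act in the same way even if the package did nothing.

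A patient who leaves against advice and dies at home is not an in-patient death in either phase, so a change in the frequency of such departures would also move the figure. At stake is whether a reported fall in mortality reflects fewer deaths or only earlier discharge.

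**Working it through.** The protocol gives no mortality figure to reproduce. The question is how far in-patient mortality can move when 30-day mortality is identical in both phases. Every mortality rate, stay and timing of death below is an assumption.

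**1. Share of 30-day deaths that fall in hospital.** Take time to death as exponential with mean m days, truncated at day 30, and discharge at day L. The in-hospital share is

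F(L) = (1 − e^(−L/m)) / (1 − e^(−30/m)).

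Move discharge from day 7 to day 5 for every patient. For m = 8: F(7) = 0.5831/0.9765 = 0.597 and F(5) = 0.4647/0.9765 = 0.476, a relative fall of 1 − 0.476/0.597 = 20%.

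| m (days) | F(7) | F(5) | Spurious fall |
|---|---|---|---|
| 5 | 0.755 | 0.634 | 16% |
| 8 | 0.597 | 0.476 | 20% |
| 12 | 0.481 | 0.371 | 23% |

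If stay lengthened from 5 to 7 days instead, in-patient mortality would appear to rise by 19% (0.755/0.634) to 30% (0.481/0.371).

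**2. Allowing for dying patients who are not discharged.** Suppose half of all 30-day deaths occur in hospital whatever the discharge practice. The share becomes 0.5 + 0.5·F(L). For m = 5 it goes from 0.878 to 0.817, a fall of 6.9%. For m = 8 and m = 12 the falls are 7.6% and 7.4%.

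**3. A smaller shift, from averted infections alone.** Section 3.11 targets absolute SSI reductions of 3, 4 and 10 percentage points in clean, clean-contaminated and contaminated surgery. If each averted SSI saves 10 days, mean stay falls by 0.3, 0.4 and 1.0 day. Putting L = 6.7, 6.6 and 6.0 after the change into F(L), against L = 7 before, gives a spurious fall of 2% to 4% for the first two strata and 7% to 11% for contaminated surgery. The allowance in step 2 reduces these to about 1% and 3% to 4%.

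**4. Other assumed stays and hazards, in numbers of deaths.** Section 3.11 gives 1630 + 1350 + 450 = 3430 patients per phase. Hold 30-day mortality at 2% in both phases and cut stay from 10 to 7 days.

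- Constant hazard, h = −ln(0.98)/30 and F(L) = 1 − e^(−hL): in-patient mortality goes from 0.67% to 0.47%. The risk ratio is 0.70, and about 7 deaths appear prevented.
- Hazard with a 7-day half-life, scaled to 2% at day 30: 1.33% to 1.06%. The risk ratio is 0.80, and about 9 deaths appear prevented.

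Over 30-day mortality of 1% to 4% and stays of 10 to 8, 10 to 7 or 8 to 5 days, the risk ratio under no true effect runs from 0.63 to 0.87. The deaths apparently prevented run from 2 to 23 per 3430 patients.

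**5. Fixed window.** With death counted to day 30 in both phases, the same scenarios give a risk ratio of 1.00 and no deaths prevented, by construction.

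**The case against.** The strongest reply is that in-patient mortality is not the protocol's only death measure. Objective 4 and endpoint 7 carry no in-patient limit. Section 4.1 records secondary outcomes at the day-30 review, and the sample-size text in Section 3.11 counts death before day 30. Endpoint 7 may well be meant as a 30-day count. This stands. A reader might infer that the day-30 contact goes unused for mortality, or that deaths after discharge would be missed altogether. The documents do not support either reading. What they show is a stay-dependent window in objective 3 and no stated window elsewhere.

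A second reply is that day-30 status is itself incomplete. Section 3.11 allows for 15% loss to follow-up or death, and Sections 3.5 and 4.1 accept later contact when day 30 is missed. In-hospital deaths are probably recorded more completely. This also stands, and is a reason to keep reporting in-hospital death beside the 30-day figure.

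A third reply is that the size is speculative. A two-day shift for every patient, if it came only from averted infections, would need about 67, 50 or 20 days saved per averted SSI (2/0.03, 2/0.04, 2/0.10). Dying patients are also seldom discharged early. Both points bring the figures down, as steps 2 and 3 show. Nor is 16% to 23% a ceiling, since other assumed stays give falls of up to 37%.

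Finally, mortality is a secondary outcome without its own power calculation, and the protocol does not call it the main safety outcome. That limits the weight of the point but does not remove it.

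**Conclusion.** The point holds for objective 3. Its mortality window depends on another outcome that the package may change, and it does not correspond to any listed endpoint. Objective 4 and endpoint 7 leave the window open. A spurious change in in-patient mortality is possible but not certain. Its direction follows the direction of any change in stay, and its size rests wholly on assumptions about stay and timing of death. Plausible values run from a few percent or less, where stay shortens only through averted infections, to 20% or more, where discharge moves by two or three days for everyone. The documents do not show that such a bias will occur or that it must favour the package. The change is worth making because a fixed window removes this artefact and the follow-up contact already exists.

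**What to change.** Use one definition in objectives 3 and 4 and endpoint 7, in both the Synopsis and the body: all-cause death within 30 days of surgery, wherever it occurs, compared between phases within each wound class. Take it from the existing day-30 contact, including LAMA patients. Section 4.1 speaks of clinical status and outcome without naming vital status, so add vital status, date of death and place of death to the day-30 page of the form. A date allows late contacts to be classified correctly against day 30. Report in-hospital death alongside the 30-day figure.

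The cost is wording and a few fields, with no additional patient contact. The downside is missing day-30 status for patients lost to follow-up, so report the number with unknown vital status by phase. The change should be made identically in both phases; if baseline collection has begun, the date of death would need to be recovered for patients already enrolled.

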## Study Duration, Enrollment and Number of Sites

### Duration of Study Participation

The study participation will last for 30-days or 90 days if implant placement during surgery. Each subject will be included in the study on pre-operative day-1 and followed till discharge. After discharge, the patient will be reviewed in the OPD or followed up telephonically till 30-days of the surgery or 90 days if implant placed (where the day of surgery will be taken as POD-0) for any evidence of surgical site infection. Any re-admission in-between the discharge and 30-days will be noted along with the reason of re-admission.

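### Readmission is defined over 30 days from discharge, but for patients without an implant it is captured only to 30 days from surgery, so the stated window is not observed and its length depends on post-operative stay

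*Protocol*

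**What the plan says.** Section 2.2 counts readmissions from discharge: the objective is the "number of hospital readmissions averted within 30 days after discharge by adoption of multipronged interventions". The synopsis uses the same window: "number of hospital readmissions averted within 30 days after discharge".

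Section 3.3.1 times follow-up from the operation, with the day of surgery as day 0. After discharge, patients are seen in clinic or "followed up telephonically till 30-days of the surgery or 90 days if implant placed". The next sentence gives the readmission rule: "Any re-admission in-between the discharge and 30-days will be noted along with the reason of re-admission". It has no 90-day extension for implants.

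Section 4.1 calls patients back at day 30. Of those who have already had an infection it says that "they will still be reviewed at 30 days after surgery to record secondary outcomes". Later contact is a fallback only: "If follow-up is not possible at 30 days after surgery, patients will be followed up as soon after this as possible".

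Section 3.8 lists "The number of ICU admissions averted and number of readmissions averted in clean, clean-contaminated and contaminated surgeries" without a time window. A separate objective in Section 2.2 is "To evaluate the impact of multipronged interventions on in-patient mortality and length of hospital stay". Section 3.9 compares phases by chi-square, t or Mann-Whitney tests, and names Kaplan-Meier, log-rank and Cox methods only for surgical site infection.

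**The concern.** The objective and the data collection start the clock at different events. Without an implant, only a patient discharged on the day of surgery has a full 30 days of observation after discharge. Readmissions after day 30 from surgery are not planned to be recorded, and a later statistical analysis plan cannot recover them.

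The shortfall equals the post-operative stay, and stay is something the trial expects may differ between phases, since it evaluates it. If stay changes, a simple before-after comparison of readmission mixes a change in risk with a change in observation time. The number averted could then be understated, overstated or given the wrong sign. In a pre-post design the baseline window cannot be reliably rebuilt once that phase has closed.

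**Working it through.** The plan gives no readmission rate, post-operative stay or sample size for readmission, so there is no figure of its own to reproduce.

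**Observed window (from the protocol).** Capture ends at day 30 from surgery. For discharge on post-operative day L:

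observed days after discharge = 30 − L.

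For L = 7 this is 23 days, and the last 7 of the stated 30 are not observed. Full observation would need follow-up to day L + 30: day 37 for L = 7, day 40 for L = 10.

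With an implant, follow-up to day 90 would cover 30 days after discharge for anyone leaving by day 60 (90 − 30). The readmission sentence still stops at 30 days, so the text does not settle which limit applies.

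**Effect of a change in stay, constant hazard (assumed).** Let R be the true 30-day post-discharge risk, equal in both phases. Then h = −ln(1 − R)/30 and observed risk = 1 − exp(−h(30 − L)). With R = 10%, h = 0.1054/30 = 0.00351 per day.

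| Post-operative stay, pre to post (assumed) | Windows (days) | Observed risk | Spurious risk ratio |
|---|---|---|---|
| 5 to 4 | 25, 26 | 8.4%, 8.7% | 1.04 |
| 7 to 5 | 23, 25 | 7.8%, 8.4% | 1.08 |
| 10 to 7 | 20, 23 | 6.8%, 7.8% | 1.14 |

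For 10 to 7 days the ratio is 1.147 at R = 5% and 1.141 at R = 15%, so R matters little. If stay lengthens, the ratio inverts: 7 to 10 days gives 1/1.14, about 0.87.

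**Readmissions clustered early (assumed).** With w = 30 − L, the captured share is (1 − exp(−w/τ))/(1 − exp(−30/τ)). For τ from 7 to 15 days:

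- 7 to 5 days: spurious ratio 1.01 to 1.03.
- 10 to 7 days: spurious ratio 1.02 to 1.07.

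**Stay falling only through averted infections.** Section 3.11 anticipates absolute reductions of 3, 4 and 10 percentage points. Assume 10 days saved per averted infection and a 7-day starting stay. Mean stay then falls by 0.03 × 10 = 0.3, 0.04 × 10 = 0.4 and 0.10 × 10 = 1.0 day. The window lengthens by 0.3/23 = 1.3%, 0.4/23 = 1.7% and 1.0/23 = 4.3%, and the spurious ratio is about 1.01, 1.02 and 1.04.

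**With a true benefit.** At a true ratio of 0.90 (constant hazard, R = 10%), the observed ratio would be 0.97 for 7 to 5 days and 1.03 for 10 to 7 days.

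These are illustrations, not bounds. A larger fall gives a larger ratio (14 to 10 days, constant hazard: 1.24).

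**The case against.** **The readmission sentence does not name its starting point.** It could be read as 30 days from discharge. But the sentence before it counts from surgery, Section 4.1 does the same, and no contact is planned that would cover the longer window.

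**A reader might infer that the package is meant to shorten stay, so that the comparison is biased against it.** The protocol does not say so. Section 2.2 evaluates the impact on stay and sets no target. Section 1.1 says infections prolong stay, which makes some shortening plausible but leaves the bias conditional. If averted infections were the only route, a 3-day fall in mean stay would need 3/0.03 = 100, 3/0.04 = 75 or 3/0.10 = 30 days saved per averted infection in the three strata. A 15% distortion is therefore not the expected case. The listed endpoint is also length of the index admission, which includes pre-operative days; only the post-operative part alters the window.

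**A reader might also infer that follow-up stops at day 30 for everyone.** It does not: implant patients are followed to 90 days, and the trial includes orthopedics and neurosurgery. For them the rule is unclear, not shown to be too short.

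**Analysis detail may sit in the statistical analysis plan.** That is fair for censoring rules and the choice of effect measure, and their absence is not held against the protocol. It does not answer the main point, because the collection window is fixed in the protocol.

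**Conclusion.** The contradiction stands. For patients without an implant discharged after the day of surgery, readmission within 30 days after discharge is not collected as stated, whether or not stay changes. For implant patients the cut-off needs to be stated.

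The bias between phases is conditional. It arises if post-operative stay differs between phases, and it works against the intervention if stay shortens and for it if stay lengthens. Its size cannot be known from the protocol. Under the assumptions shown, the spurious risk ratio runs from about 1.01 (stay falling by a fraction of a day, or early-clustered readmissions) to about 1.15 (10 to 7 post-operative days, constant hazard).

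This affects the readmission half of one secondary endpoint, for which no power is claimed. The primary endpoint is untouched.

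**What to change.** Use one readmission window, stated identically in the synopsis and Sections 2.2, 3.3.1, 3.8 and 4.1, for all patients, with or without an implant, and in both phases. Either:

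- **(a) Count from surgery.** Restate the objective and endpoint as readmission within 30 days after surgery. Make sure the case record form holds the discharge and readmission dates, and account for time at risk from discharge; restating alone would leave the window dependent on stay. The cost is an amendment and possibly a form change: Section 3.3.1 mentions the reason for readmission but no date, so the form must be checked.
- **(b) Count from discharge.** Keep 30 days after discharge and time a telephone contact to that day, retaining the day-30 review from surgery for the primary endpoint. The cost is a later call per patient, at most 3260 + 2700 + 900 = 6860 calls at the planned sample size. Telephone follow-up is already foreseen and a project nurse is budgeted for follow-up. With both phases observed for 30 days, the spurious ratio from the window is 1.00 whatever the stay.

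The choice should be made before baseline follow-up closes.
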